The CD colonization status will be documented by culture of stool or rectal swabs collected on days 0 and 15. The stool or rectal swab samples will be subjected to glutamate dehydrogenase (GDH) and toxin assay (by enzyme immunoassay, EIA) tests for the participants with suspected CDI. The samples positive for GDH and/or toxin shall be subjected to a nucleic acid amplification test (NAAT). In confirmed cases of CDI, culture for CD (using selective media and anaerobic gas pack) shall be done. The positive culture isolates shall be subjected to VITEK-2 for antimicrobial susceptibility testing (AST). The sample aliquots shall be stored at -80°C for further analysis.

The CD-positive isolates from 30 participants (10 each of those who acquired CD, who eliminated CD, and who had confirmed CDI) shall be subjected to whole genome sequencing. The fecal cytokines (e.g., CXCL-5, CXCL-8) and lactoferrin shall be estimated by enzyme-linked immunosorbent assay (ELISA) kit in a subset of 25 participants per group from stool or rectal swab samples collected on days 0 and 15. The *Torani* product samples will be cultured to detect microbiota (e.g., *Lactobacillus* species), followed by the bacteria species identification (16S rRNA gene amplification) and analysis of SCFAs by high-performance liquid chromatography (HPLC).

Statistical analysis

Sample Size Calculation

A study documented that probiotic consumption reduced CDI by approximately 70% [27]. Assuming that the *Torani*-xylitol mix shall reduce the CD colonization from 15% to 5% in hospitalized participants at discharge, the estimated sample size is 196 participants (98 per group) with a 95% confidence level and 80% power. Thus, we propose to include 200 participants (100 per group).

Data Analysis

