The normality of the data distribution will be gauged using the Shapiro-Wilk test. The continuous variables will be expressed as mean and standard deviation or median and interquartile range based on the distribution pattern. The categorical variables will be expressed as frequency and proportion. Missing data will be addressed using various imputation techniques, and sensitivity analyses will be conducted to assess the robustness of the results. The quantitative data with normal distribution will be compared using the unpaired t-test, and those with skewed distribution will be analyzed using the Mann-Whitney U test. The categorical data will be compared using the chi-square or Fisher's exact test, as applicable. Analysis of variance (ANOVA) or the Kruskal-Wallis test shall be considered for the multiple comparisons. A p-value of < 0.05 will be considered significant. For the study outcomes, results will be summarized in absolute (risk difference or mean difference) and relative (risk ratio) effect size measures along with their 95% confidence intervals. Regression analysis shall be done to identify the factors that influence CD colonization or infection and their strength of association. A per-protocol (PP) analysis will be performed to assess efficacy. The safety analysis will be done using the intent-to-treat (ITT) principle. R software (version 4.5.0 or higher) will be used for the data analysis and generation of plots [28].

Interim Analysis

One interim analysis is proposed after enrollment of 50% (n = 100) of participants and completion of the day-15 data. The interim analysis will be conducted using the O’Brien-Fleming spending function and a type I error rate of 5%.

Ethical Consideration and Trial Registration

The Institutional Ethics Committee of KIMS, Bhubaneswar, has approved the study protocol (KIIT/KIMS/IEC/1753/2024). The trial has been prospectively registered with the Clinical Trial Registry of India (CTRI/2025/03/083479). The study will comply with the Good Clinical Practice (GCP), the Declaration of Helsinki, and institutional norms. All the participants will be recruited for the study after obtaining written informed consent, and their privacy and confidentiality will be maintained.

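### For the faecal markers measured on days 0 and 15 in 25 per group, the plan names no baseline-adjusted analysis and leaves open whether the day-15 value or the change is compared

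*Protocol article*

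**What the plan says.** Under Outcome Assessment (Materials and methods), the protocol article plans ELISA assays of faecal cytokines and lactoferrin. They are to be done "in a subset of 25 participants per group from stool or rectal swab samples collected on days 0 and 15". Each marker in this subset therefore has a planned baseline and a planned post-treatment value.

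Under Data Analysis, one rule covers all continuous data. First, "The normality of the data distribution will be gauged using the Shapiro-Wilk test". Then "The quantitative data with normal distribution will be compared using the unpaired t-test". If the data fail that check, the alternative is a rank test: "those with skewed distribution will be analyzed using the Mann-Whitney U test". Regression appears in that section only as a way to find what is associated with *C. difficile* colonisation or infection, not as an analysis of the markers. The section does not mention the markers by name and does not say which quantity, the day-15 value or the change from day 0, enters the test.

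For study outcomes the section adds that "results will be summarized in absolute (risk difference or mean difference) and relative (risk ratio) effect size measures along with their 95% confidence intervals". The outcome measures listed in the Discussion are colonisation, incidence of infection, the profile of the organism, and product safety. The faecal markers are not among them.

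**The concern.** With 25 per group, precision is scarce. A baseline measurement of the same marker is usually the most useful covariate available, and here it is already planned. A two-sample test on the day-15 value ignores it. A two-sample test on the change uses it with a fixed coefficient of one, which is inefficient when the two measurements are only moderately correlated. The document chooses neither, and nothing it names does better than both.

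There is a second, smaller issue. The test is chosen after a preliminary look at the distribution, so the form of the result is not fixed beforehand: a difference in means if the t-test is used, a rank comparison if Mann-Whitney is used.

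At stake are the width of the confidence intervals for the marker comparisons and how clearly the result can be interpreted. The colonisation and infection results are not affected.

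**Working it through.** **Inputs from the protocol article.** 25 per group; days 0 and 15; unpaired t-test or Mann-Whitney after Shapiro-Wilk; significance at 0.05 (taken as two-sided). The article gives no sample size or power figure for this subset, so there is no figure of its own to reproduce.

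**Assumption.** The day 0 to day 15 correlation r is not in the article. It is varied over 0.3, 0.5 and 0.7, with equal SDs on the two days, on the scale analysed.

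**Variance of the arm difference, relative to day-15 only.**
- Day-15 value only: 1
- Change score: 2(1 − r)
- ANCOVA: 1 − r², apart from one degree of freedom

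**Effective size of 25 per group under ANCOVA.**
- Against day-15 only: 25/(1 − r²)
- Against change: the variance ratio is (1 − r²)/[2(1 − r)] = (1 + r)/2, so the effective size is 50/(1 + r)

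| Assumed r | 25/(1 − r²) | 50/(1 + r) |
|---|---|---|
| 0.3 | 25/0.91 = 27.5 | 50/1.3 = 38.5 |
| 0.5 | 25/0.75 = 33.3 | 50/1.5 = 33.3 |
| 0.7 | 25/0.51 = 49.0 | 50/1.7 = 29.4 |

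The two columns cross at r = 0.5, where 2(1 − r) = 1 and the change score and the day-15 value are equally precise. Below 0.5 the change score is the worse of the two; above 0.5 the day-15 value is.

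**Detectable difference and power.** With 25 per group and two-sided 0.05, the noncentral t distribution gives 0.81 SD detectable at 80% power for the day-15 value alone, and 41% power for a difference of 0.5 SD. Under ANCOVA the detectable difference is 0.809 × √(1 − r²):

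| Assumed r | Detectable at 80% power | Power for 0.5 SD |
|---|---|---|
| day-15 only | 0.81 SD | 41% |
| 0.3 | 0.77 SD | 44% |
| 0.5 | 0.70 SD | 52% |
| 0.7 | 0.58 SD | 68% |

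**Choice of test by Shapiro-Wilk.** This was simulated with 5,000 trials per distribution, 25 per arm, no true difference, Shapiro-Wilk at 0.05 in each arm, and Mann-Whitney used if either arm failed.

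| Distribution | Mann-Whitney chosen | Type I error of the two-step rule |
|---|---|---|
| Normal | 10% | 0.051 |
| Lognormal, log-SD 0.3 | 52% | 0.055 |
| Lognormal, log-SD 0.5 | 87% | 0.055 |
| Lognormal, log-SD 1 | nearly 100% | 0.046 |

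The error rate stays near 5% throughout. The choice is close to a coin toss only for mild skew; marked skew is detected reliably at this sample size.

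**The case against.** The strongest reply is that this is a condensed article, that an unadjusted comparison of randomised arms is valid, and that covariates and transformations for subset markers are commonly settled in an analysis plan. Much of that stands. It is why the point is about a better choice of method and not about an error. It does not remove the point, because the article does state a rule for continuous data, and that rule suits a marker with a planned baseline less well than an equally simple alternative.

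Four stronger readings are tempting, and the document supports none of them.

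- *The plan discards the baseline.* It does not say so. An unpaired test on within-person changes fits the stated rule and uses day 0. The gain to 49 at r = 0.7 applies only against a day-15-only analysis; against change it is 29.
- *The normality test distorts the error rate, or has too little power to be useful.* The simulation shows neither, except that the choice is unstable under mild skew.
- *Mann-Whitney contradicts the promised mean difference and CI.* That promise is made for study outcomes, and the Discussion's list omits these markers. A mean difference could also be reported alongside a rank test.
- *Stool and swab results are pooled without regard to specimen type.* The article allows either specimen but gives no rule on combining them.

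**Conclusion.** The point holds as a minor improvement. For the faecal markers, the article names only an unadjusted two-sample test selected by Shapiro-Wilk. It names no baseline-adjusted analysis and leaves the compared quantity open. Either reading of the rule is valid and either loses precision: the equivalent of about 2, 8 or 24 participants per group against day-15 only, or about 13, 8 or 4 against change, at r = 0.3, 0.5 or 0.7 (the effective sizes above minus 25).

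These sizes rest on assumed correlations and on equal SDs on the two days, and they ignore the one degree of freedom spent on the covariate. The true correlation could be low, in which case the gain over a day-15-only analysis would be small. Nothing here bears on colonisation, infection or safety.

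**What to change.** For the faecal cytokines and lactoferrin, state before any values are seen that:

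- the analysis is ANCOVA of the log day-15 value on arm and log day-0 value;
- the result is the adjusted geometric mean ratio with its 95% CI;
- the Shapiro-Wilk selection step does not apply to these markers.

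Leave day-15 specimen type out of the main model. It is determined after randomisation and could be affected by the product through bowel function, so adjusting for it could remove or distort part of the effect. Examine stool versus swab in a sensitivity analysis only.

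The cost is a few lines of wording. No new samples, participants or assays are needed, and the article reports that the study has not yet started.

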## Introduction

*Clostridioides difficile* (also known as *Clostridium difficile*) infections (CDI) are linked to extended hospital stays and fatalities, particularly in the elderly population [1]. Though CDI is considered a nosocomial infection, community-based transmission among older adults is common [2]. An increase in CDI incidence has been observed in American, European, and certain Asian hospitals over time. This tendency can be attributed to the increasing antibiotic usage and the emergence of novel, hypervirulent strains [3-6]. In parallel with the rising CDI incidence, the antibiotic resistance pattern and associated mortality have also increased [7].

*Clostridioides difficile* (CD) usually spreads by the fecal-oral route and causes exotoxin-mediated illness. In India, CDI affects 3.4-18% of people, with older adults having a greater risk [8]. While 3-15% of healthy persons may have CD in their normal flora, 16-35% of hospitalized patients may have asymptomatic colonization [9,10]. The most significant risk factor for CDI is the use of antibiotics. The antibiotic class and its exposure duration determine the infection likelihood [11].

The resistance of the bacterial spores to heat and disinfectants contributes to the spread of CDI in hospitals. CDI ranges from mild diarrheal symptoms to fatal colitis [3,12]. Nowadays, community-acquired colitis is more prevalent owing to CDI and infective diarrhea [12]. Recurrent CDI (rCDI) increases morbidity, mortality, and healthcare costs and dampens the quality of life [3,12,13]. A recent meta-analysis shows 8.3 CDI cases for every 10,000 patient days [13]. Complex carbohydrate conversion by the normal colonic microbiota is essential to elicit resistance to invading microorganisms [14]. Gut microbiomes digest complex carbohydrates, starch, and dietary fiber to create short-chain fatty acids (SCFAs). SCFAs modulate inflammation and the immune system by lowering T and B cell differentiation and migrating immune cells (i.e., neutrophils, dendritic cells, and macrophages) [15].

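### Day-0 colonisation is cultured but not used in the only between-arm test named for colonisation, which gives up precision and protection against chance imbalance

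*Protocol article*

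**What the plan says.** Under Outcome Assessment, colonisation status is established by culture of stool or rectal swabs "collected on days 0 and 15". The eligibility criteria do not exclude participants who already carry the organism, and they admit patients within 48 hours of admission. Randomization and Blinding describes 1:1 permuted blocks of 4 and 6, with no stratification factor stated.

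The sample size rests on the product being able to "reduce the CD colonization from 15% to 5% in hospitalized participants at discharge". That target is total colonisation at the end, whatever the status at entry.

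Under Data Analysis, "The categorical data will be compared using the chi-square" or Fisher's exact test, with a risk difference, a risk ratio and 95% confidence intervals. No baseline term is named. Regression is mentioned once, to find the factors that influence colonisation or infection, and not to estimate the treatment effect. Acquiring and eliminating the organism appear only as a way of choosing isolates for sequencing.

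On how common carriage is, the Introduction gives 3-15% for healthy persons and says that "16-35% of hospitalized patients may have asymptomatic colonization".

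**The concern.** The day-0 culture is the baseline value of the outcome itself. Someone positive at entry can be positive at day 15 by persistence; someone negative can be so only by acquisition. If these two probabilities differ much, day-0 status explains part of the outcome variation, and a comparison that ignores it leaves that part in the error.

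With about 100 per arm and no stratification by carriage, the arms can also differ at entry by an amount that is not small beside a 10-point target. The unadjusted analysis cannot correct for that in the trial actually run. At stake is some power, and how convincing the result will be if the baseline table shows unequal carriage.

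**Working it through.** **The plan's own figure.** The article says "the estimated sample size is 196 participants (98 per group) with a 95% confidence level and 80% power". For 15% v 5%, two-sided 5% and 80% power, the pooled normal formula gives 141 per group (138 unpooled, 133 arcsine, 160 with continuity correction), not 98. By formula, power is about 65% at 98 and 66% at 100 per group. The shortfall is a separate matter and adds no weight here. It only explains why the unadjusted power below is not 80%. (The simulated Pearson chi-square test gives 68% rather than 66% because the formula is approximate.)

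**Step 1: chance imbalance at entry.** Inputs: 100 per arm (Sample Size Calculation) and day-0 carriage *p*, which is an assumption. The values span 5-10%, within the range for healthy persons, and 16-35%, the range for hospitalised patients. The standard deviation of the arm difference is √(2p(1−p)/100), and the chance of a gap over 5 points is 2[1 − Φ(0.05/SD)].

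| Carriage *p* | SD (points) | 0.05/SD | Chance of gap over 5 points |
|---|---|---|---|
| 5% | 3.1 | 1.62 | 10% |
| 10% | 4.2 | 1.18 | 24% |
| 16% | 5.2 | 0.96 | 33% |
| 35% | 6.7 | 0.74 | 46% |

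Counts are whole numbers, so the normal figure lies between two exact binomial ones. For 6 points or more they are 7%, 19%, 29% and 42%; for 5 points or more, 14%, 29%, 38% and 51%.

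**Step 2: what a 5-point gap does.** The shift in the follow-up difference is the gap times (persistence − acquisition). At 16% carriage with 15% positive at follow-up, acquisition is (0.15 − 0.16 × persistence)/0.84.
- Persistence 50%: acquisition (0.15 − 0.08)/0.84 = 8.3%; shift 5 × (0.50 − 0.083) = 2.1 points.
- Persistence 70%: acquisition (0.15 − 0.112)/0.84 = 4.5%; shift 5 × (0.70 − 0.045) = 3.3 points.

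Those are values under no treatment effect. If the product cuts both rates to one third and the gap is split evenly between the arms, they become 2.5 × 0.417 × (1 + 1/3) = 1.4 and 2.5 × 0.655 × (1 + 1/3) = 2.2 points. The shift may favour either arm.

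**Step 3: power.** Simulation with 100 per arm, 15% positive in controls at follow-up, relative risk 1/3 in carriers and non-carriers alike, two-sided 5%, 200,000 trials per setting. Unadjusted chi-square power is 68% in every setting. Power of the Cochran-Mantel-Haenszel (CMH) test stratified by day-0 status:

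| Carriage | Persistence: stratified power |
|---|---|
| 5% | 30%: 67%; 50%: 68%; 70%: 70% |
| 10% | 30%: 68%; 50%: 70%; 70%: 74% |
| 16% | 30%: 68%; 50%: 72%; 70%: 81% |
| 25% | 30%: 69%; 40%: 72%; 50%: 77% |
| 35% | 25%: 68%; 35%: 72% |

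The change runs from about −1 to +13 points. The largest gain, at 16% carriage and 70% persistence, implies acquisition of only 4.5% in non-carriers. At 35% carriage, 50% persistence cannot occur with a 15% control rate, since 0.35 × 0.50 = 17.5%.

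**Step 4: false positives.** Under no effect (5-15% carriage, 60-80% persistence), the unadjusted test rejects in 5.0-5.2% of all trials. Among trials where the control arm happens to have at least 5 more carriers, it rejects in 7-12%; the stratified test stays near 5%.

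**Step 5: restricting to non-carriers.** In four settings with 5-15% carriage, 60-80% persistence and the same effect in both strata, testing day-0 negatives alone gives 30-57% power against 68% for all participants. Stratifying everyone is the safer choice.

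**The case against.** **The sentence is generic, and an analysis plan not shown may adjust.** It is written by data type, the article is condensed, and nothing in it forbids a covariate. This is fair, and it keeps the point to a recommendation. But the article does name a method for comparing categorical data, and that method has no baseline term. The regression has a different stated purpose and does not fill the gap.

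**The unadjusted test is valid.** This stands. Over all randomisations, its p-value and confidence interval already allow for chance imbalance (Step 4). A reader might infer that the planned analysis is biased; it is not. This holds for participants analysed as randomised. The per-protocol efficacy set is a separate question.

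**Mixing clearance with acquisition is no defect.** This also stands. A reader might infer that pooling the two defeats an outcome meant to show prevention. The Discussion does speak of prevention, but the sample-size target is total colonisation at discharge, and both processes belong in that.

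**The document does not give carriage at entry.** Correct. A reader might apply 16-35% directly to the 200 participants, but that range describes hospitalised patients in general, while entry is within 48 hours of admission. Entry carriage could be nearer the range for healthy persons, where the chance of imbalance and the gain in power are smaller.

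**Infection at entry.** A reader might add that infection already present on day 0 could be counted as an event. The Discussion names infection incidence as the outcome, which already largely means new cases; the detailed definition is what an article commonly leaves out.

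**Conclusion.** The point holds as a missed improvement in efficiency and robustness, not as an error of validity. A baseline value of the outcome is collected, and the only between-arm comparison named does not use it.

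Its size depends on two quantities that must be assumed: carriage at entry and persistence among carriers. Over 5-35% carriage, the chance of a gap over 5 points is about 10% to 46%. Over the carriage and persistence settings tried, stratified power lies between 67% and 81%, against 68% unadjusted. At low carriage or low persistence the gain is close to nil; no setting showed a material loss. These power figures assume the same relative effect in carriers and non-carriers.

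**What to change.** In Data Analysis, prespecify that the efficacy comparison of day-15 or discharge colonisation is stratified by, or adjusted for, day-0 culture result. Either of these would do:
- Mantel-Haenszel risk difference and risk ratio with 95% confidence intervals and a CMH test, stratified by day-0 status; or
- logistic regression on arm and day-0 status, with standardised risks used to report the risk difference and risk ratio.

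Keep day-0 carriers in this comparison. Report acquisition among day-0 negatives and clearance among day-0 positives, by arm, as secondary results. State that the regression to identify factors is separate from the treatment comparison.

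The cost is wording only: the day-0 culture is already planned, no sample or visit is added, and the study has not started.

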## Results

Since the study has not commenced, the results have yet to be obtained. The flow of this RCT has been illustrated in Figure 1.

**Figure 1 FIG1:**
[figure not shown]
CONSORT diagram CD: *Clostridioides difficile* (also known as *Clostridium difficile*), CDI: CD infection, CONSORT: consolidated standards of reporting trial.

## Discussion

This RCT has been designed to document the effect of the *Torani*-xylitol mixture on CD colonization and CDI by modulating gut microbiota among hospitalized elderly patients. The outcome measures are CD colonization, CDI incidence, CD profile (genotype, phenotype, and AST) of CD, and safety of the investigational product. As gut dysbiosis is an important causative factor for CDI, the probiotic-prebiotic-synbiotic products have potential roles [11,14]. The traditional probiotic-rich foods like *Torani* (fermented rice water) in Odisha provide advantages in their acceptability, ease of preparation, availability and use, and affordability. The components of *Torani*, like SCFA and enrichment with prebiotic (xylitol), are likely to repair gut dysbiosis, modulate colonic milieu, improve gut immunity, and prevent CD colonization and CDI [14,15,17,19].

This study has a few limitations. First, the study design is an open-label RCT, owing to the nature of the intervention. Allocation concealment will be done to mitigate the performance and detection bias. Second, the duration of therapy is fixed for all participants irrespective of the group, gender, disease, or hospitalization duration. Third, we could not get the exact power analysis for this study, as this is the first study to document the effect of the *Torani*-xylitol mixture on CD colonization and CDI.

